## Abstract

**Background:** Sepsis commonly causes acute respiratory distress syndrome (ARDS), and ARDS contributes to poor prognosis in sepsis patients. Early prediction of ARDS for sepsis patients remains a clinical challenge. This study aims to develop and validate chest computed tomography (CT) radiomic-based signatures for early prediction of ARDS and assessment of individual severity in sepsis patients. **Methods:** In this ambispective observational cohort study, a deep learning model, a sepsis-induced acute respiratory distress syndrome (SI-ARDS) prediction neural network, will be developed to extract radiomics features of chest CT from sepsis patients. The datasets will be collected from these retrospective and prospective cohorts, including 400 patients diagnosed with sepsis-3 definition during a period from 1 May 2015 to 30 May 2022. 160 patients of the retrospective cohort will be selected as a discovering group to reconstruct the model and 40 patients of the retrospective cohort will be selected as a testing group for internal validation. Additionally, 200 patients of the prospective cohort from two hospitals will be selected as a validating group for external validation. Data pertaining to chest CT, clinical information, immune-associated inflammatory indicators and follow-up will be collected. The primary outcome is to develop and validate the model, predicting in-hospital incidence of SI-ARDS. Finally, model performance will be evaluated using the area under the curve (AUC) of receiver operating characteristic (ROC), sensitivity and specificity, using internal and external validations. **Discussion:** Present studies reveal that early identification and classification of the SI-ARDS is essential to improve prognosis and disease management. Chest CT has been sought as a useful diagnostic tool to identify ARDS. However, when characteristic imaging findings were clearly presented, delays in diagnosis and treatment were impossible to avoid. In this ambispective cohort study, we hope to develop a novel model incorporating radiomic signatures and clinical signatures to provide an easy-to-use and individualized prediction of SI-ARDS occurrence and severe degree in patients at early stage.

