## 2. Materials and Methods

### 2.1. Study Design

The study was registered with ClinicalTrials.gov (NCT04541264, https://clinicaltrials.gov/show/NCT04541264) on 9 September 2020. In this double-center, ambispective, observational study, we will collect chest CT and clinical information of patients with sepsis and septic shock treated in our hospital (Sun Yat-sen Memorial Hospital, Sun Yat-sen University) and Shenshan Medical Center, Memorial Hospital of Sun Yat-sen University (from 1 May 2015 to 30 May 2022). For the final analysis, 400 patients will be enrolled according to the TRIPOD guideline [19]. Among the 400 patients, 200 will be retrospectively recruited from our hospital from May 2015 to August 2020, 100 patients will be prospectively recruited from our hospital from August 2020 to May 2022, and the other 100 patients will be prospectively recruited from Shenshan Medical Center, Memorial Hospital of Sun Yat-sen University from August 2020 to May 2022. One hundred-sixty patients of the retrospective cohort will be selected as a discovering group to reconstruct the model, and 40 patients of the retrospective cohort will be selected as a testing group for internal validation. Additionally, 200 patients of the prospective cohort will be selected as a validating group for external validation. Follow-up of the relevant patients will be conducted until April 2023. This study was approved on 19 August 2020 by the Ethics Committee of Sun Yat-sen Memorial Hospital, Sun Yat-sen University, Guangzhou, China. Figure 1 shows the flow chart of the study protocol.

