We intend to employ modified ResNeSt [24], DenseNet [25] and EfficientNet [26] models to train a robust model. All networks will use 3D convolution, ReLU/LeakyReLU nonlinear activation function and batch normalization. For the entire CT image and the outlined region of interest, we will train two convolutional neural networks to extract features. For the ROI, we will randomly sample the voxels containing 80% of the ROI from the entire CT image to generate an image. We will perform five-fold cross-validation on the training set in model training phase, and use random rotation, translation and transposition data enhancement strategies to increase the data and reduce the imbalance between classes. Additionally, the network will adopt the cross-entropy loss as a loss function, Xavier as initialized parameter and stochastic average gradient descent as optimizer. In the last fully connected layer of the network, we will modify the corresponding structure by adding pre-processed clinical variables and other data, and finally predicted whether ARDS might occur.

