### 2.7. Statistical Analysis

Continuous variables between two groups will be compared by T test or Wilcoxon rank sum test, whereas categorical variables will be compared by χ^2^ test. Univariate and multivariate logistic regression will predict occurrence of ARDS, using variables that selected by consensus of variable importance ranking by random forest [28] and least absolute shrinkage and selector operation (LASSO) regression techniques [29]. With the selected clinical and radiomics features, we will develop two versions of the ARDS prediction model, using logistic regression (LR) and support vector machine (SVM). Then a prognostic model will be built for prediction of individual and classification of severe level. ROC curves will determine the optimal cut-off point for models, and patients will be divided into high-risk and low-risk groups. VFD, RFFD and 28-day mortality will be screened indicators with LASSO-COX and RFE-SVM algorithm. Thereafter, these will be estimated using the Kaplan–Meier method. All these algorithm performances will be assessed using the AUC and *p*-values less than 0.05 will be considered statistically significant. After these main analyses, other subgroups will be carried out as following: septic shock vs. non-septic shock, and pulmonary sepsis vs. non-pulmonary sepsis. Statistical analysis will be performed using the R programming language, including its packages.

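### CT features learned from the discovery patients' own ARDS labels enter second-stage models for the same outcome, with no statement that they are out-of-fold; if they are not, CT is over-weighted

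*Protocol article*

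**What the plan says.** Four places in the protocol article, read together, describe a two-stage model.

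- **Abstract.** The network is the source of the features: a "prediction neural network, will be developed to extract radiomics features of chest CT from sepsis patients".
- **Section 2.5.** "For the entire CT image and the outlined region of interest, we will train two convolutional neural networks to extract features". Training is supervised, since "the network will adopt the cross-entropy loss as a loss function". Weights start from Xavier initialisation and no pre-training is mentioned. The last layer is modified by "adding pre-processed clinical variables and other data, and finally predicted whether ARDS might occur". Five-fold cross-validation is planned, for the network training phase.
- **Section 2.7.** Variables are chosen by random forest importance and LASSO and go into univariate and multivariate logistic regression for ARDS. "With the selected clinical and radiomics features, we will develop two versions of the ARDS prediction model", by logistic regression and SVM. The significance threshold is 0.05.
- **Section 2.1.** 160 retrospective patients "will be selected as a discovering group to reconstruct the model". No separate sample is named for learning the features. A further 40 retrospective and 200 prospective patients are set aside for internal and external validation.

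The article does not say whether the CT values entering section 2.7 come from networks that had seen the patient's own label.

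**The concern.** Logistic regression tests and LASSO penalties take the covariates as fixed without sight of the outcome. A feature from a network trained on ARDS, evaluated in its own training patients, already carries part of their ARDS labels. The second stage then partly measures how well a flexible network can fit 160 labels, and not what CT adds to the clinical data.

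This is distinct from optimism after variable selection. The leak arises when the covariate is built, so it would remain with one pre-chosen CT feature and no selection. It affects the coefficients as well as the p-values.

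At stake is the model itself, which is the study's primary aim. If CT looks stronger in the discovery group than it is, it receives too much weight, and the combined model sent to validation can be worse than the clinical variables alone. A cut-off set on discovery scores would be distorted too.

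**Working it through.** **1. The plan's own figure.** Section 2.3 gives about 20 variables and 5–10 patients per variable: 20 × 5 = 100 and 20 × 10 = 200. The stated minimum of 160 equals 20 × 8, so it is compatible with these inputs but not fixed by them. At 25–50% ARDS, 160 patients give 40–80 events. The 160 is not contested here; it sets the size of the check.

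**2. The two versions compared.** Second stage: logit P(ARDS) = a + b·clinical + c·s.
- Same-patient score: s(i) = f(CT(i)), with f trained on all 160 patients, including i.
- Out-of-fold score: s(i) = f₋ₖ(CT(i)), with f₋ₖ trained on the four folds that exclude i, that is 160 × 4/5 = 128 patients.

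From the article: 160 development and 200 validation patients, five folds, ARDS rate 25–50%, threshold 0.05 (taken as two-sided). Assumed, because the article gives no figure: clinical effect sizes, number of CT inputs and learner capacity.

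**3. Simulation A: ridge-logistic learner, one clinical score, pure-noise CT, 200 runs per setting.** Clinical alone gives a validation AUC of about 0.73. Columns run from low to high capacity.

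| Same-patient CT score | | | | | |
|---|---|---|---|---|---|
| ARDS 25%: training AUC of CT | 0.61 | 0.66 | 0.74 | 0.86 | 0.996 |
| CT significant (%) | 47 | 91 | 100 | 100 | 91 |
| Validation AUC, combined | 0.71 | 0.69 | 0.65 | 0.60 | 0.55 |
| ARDS 50%: training AUC of CT | 0.59 | 0.64 | 0.71 | 0.83 | 0.99 |
| CT significant (%) | 39 | 88 | 99.5 | 100 | 98 |
| Validation AUC, combined | 0.71 | 0.70 | 0.67 | 0.61 | 0.55 |

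Rejection dips at the highest capacity because the logistic fit nears separation. With out-of-fold scores, validation AUC is 0.72–0.73 in all settings.

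**4. Simulation A with real CT signal** (training AUC 0.86–0.89): validation AUC is 0.65–0.66 with same-patient scores, 0.71–0.72 out-of-fold and about 0.71 for clinical alone. The harm is not confined to useless CT.

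**5. Simulation B: a small leaky-ReLU network, Xavier start, cross-entropy loss, three real clinical predictors, pure-noise CT, 80 trials per setting.** Same-patient scores, with clinical-only results in brackets:

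| | Light fit | Moderate fit | Heavy fit |
|---|---|---|---|
| CT AUC, development | 0.70 | 0.94 | about 1.00 |
| CT significant, rank test (%) | 95 | 100 | 100 |
| CT significant, multivariable (%) | 91 | 99–100 | not usable |
| Random forest ranks CT first (%) | 55 | 100 | 100 |
| Clinical predictors significant, of 3 | 2.74 (2.80) | 1.5–1.6 (2.7–2.8) | not usable |
| Clinical predictors kept by LASSO, of 3 | 3.0 (3.0) | 2.9 (3.0) | 1.1–2.1 (3.0) |
| AUC, development | 0.83 | 0.96 | 1.00 |
| AUC, 200 new patients | 0.71 (0.77) | 0.59–0.61 (0.77) | 0.56–0.57 (0.76) |

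LASSO kept CT in 100% of trials in every column. Under heavy fit, 63–66% of the multivariable models could not be fitted, and Wald tests in the rest were significant in 0–15%; separation makes those p-values meaningless.

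Out-of-fold, random forest ranked CT first in 0–1% of trials, and AUC in new patients was 0.76–0.77, as for clinical-only. LASSO still kept noise CT in 74–84%, so retention by LASSO is no evidence for CT even then.

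**6. Is an out-of-fold p-value valid?** No. In repeats of simulation A with noise CT, two-sided rejection with out-of-fold scores was about 12–23% against a nominal 5%. Counting only positive effects gives 1–7%, which hides the excess. Simulation B gave 4–20%. The reason is that each patient's label helped train the networks that scored the other folds, so scores and labels are not independent across patients.

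**The case against.** The strongest objection is that the article never says same-patient features are used. It plans five-fold cross-validation, and a condensed article may leave to a fuller document which values are exported. If out-of-fold values were exported, the problem would largely disappear. This stands to the extent that the point must be conditional. It does not remove the point: the article fixes the two-stage flow on one group of 160, confines cross-validation to network training, and deep feature vectors from five separately trained networks are not aligned, so they could not simply be pooled.

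The pipeline is also partly inferred. The network in section 2.5 takes clinical variables itself and predicts ARDS end to end, and section 2.3 draws its roughly 20 variables from radiomic features with reference to a previous study, which leaves some room for hand-crafted features. Such features would not carry this leak. But no hand-crafted extraction is described in sections 2.5 or 2.7, and the Abstract and section 2.5 name the network as the extractor.

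A reader might infer that the study will declare CT a significant predictor whatever the truth, or that its validation is compromised. The documents support neither. The Abstract evaluates the model by AUC, sensitivity and specificity in internal and external validation, and the 0.05 threshold is a general clause. A model spoiled in this way would show a poor AUC in the 200 prospective patients, provided they are kept out of training. Validation would reveal the damage but not repair it.

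The Discussion concedes overfitting from small sample size and high-dimensional features. That does not cover the reuse of labels.

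**Conclusion.** The point holds in conditional form. As written, the plan learns CT features from the discovery patients' ARDS labels and reuses them for the same outcome without saying they are out-of-fold. If same-patient features are used, uninformative CT can appear significant in the discovery group (39–100% of runs in simulation A), and the combined model can lose about 0.02 to 0.2 in AUC against clinical variables alone (0.73 to 0.71 at the mildest fit, 0.76 to 0.56 at a heavy one).

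It would go too far to say that real clinical predictors are always displaced. Under light fit the number significant barely moved (2.74 against 2.80 of 3), although AUC in new patients still fell from 0.77 to 0.71. Marked displacement needs a closer fit, and the article does not state network capacity.

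The sizes rest on assumed clinical effects and on simple learners. Neither simulation ran a 3D convolutional network, image augmentation or an SVM. The direction was the same for both learners and across the ARDS rates examined.

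**What to change.** In sections 2.5 and 2.7, state that:

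- for discovery patients, the CT input to random forest, LASSO, logistic regression and SVM is an out-of-fold score, with each patient scored by the network trained on the four folds that exclude that patient;
- the score comes from a CT-only output of each network (whole CT and ROI), taken before clinical variables are added in the last layer, because the final score already mixes CT with clinical data and would count the latter twice;
- scores are used, not deep feature vectors;
- the networks are refitted on all 160 patients only to score the testing and validating groups;
- no p-value for CT is reported from the discovery group, whether same-patient or out-of-fold, and CT's added value over clinical variables is assessed in the prospective cohort.

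Cost: the five-fold networks are already planned, so saving their held-out scores needs little extra computing and no extra patients. A CT-only output must be defined, which is a small design change and not only wording. Discovery-group performance will look less favourable, and because the fold networks train on 128 patients instead of 160, their scores are slightly conservative.

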### 2.6. Outcome Measures

In this study, the primary outcome measure will be occurrence of ARDS, which is defined as pulmonary or nonpulmonary sepsis that had progressed into ARDS.

Secondary outcome measures are as follows:

(1)Grade of pulmonary damage: patients will be classified as mild (200 <  PaO2/FiO2 ≤ 300 mmHg), moderate (100 < PaO2/FiO2 ≤ 200 mmHg), or severe (PaO2/FiO2  ≤  100 mmHg) at the moment of diagnosis of ARDS [2];(2)Ventilator-free days, VFD: defined as the number of days between successful weaning from mechanical ventilation and day 28 after ICU admission;(3)Respiratory organ failure-free days, RFFD: defined as the number of days between a day without evidence of respiratory organ failure [27];(4)28-day mortality: all-cause mortality within 28 days following enrolment.

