### 2.4. Data Collection

All clinical data will be collected by investigators and trained personnel. Each participant’s data will be filled in electronic case report forms (CRF) and stored online using research electronic data capture (REDCap) [23]. The CRF is designed to collect the necessary information based on this study protocol. The detailed contents of CRF contain four main parts: (1) demographics and chronic disease history (including age, gender, smoking status, hypertension, diabetes mellitus, chronic lung disease and coronary heart disease), (2) laboratory tests and imaging examination (including routine blood, routine biochemistry, coagulation function, arterial blood gas analysis, blood culture, sputum culture, and ID of chest CT), (3) treatment process (including source of infection, anti-infection therapy, ventilator use or not, and type and dose of vasopressor therapy), (4) outcomes (intensive care unit (ICU) stay or not, length of ICU stay, total length of hospital stay, and in-hospital death).

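### Ventilator-free days as printed credits days after death and leaves many patients without a value, RFFD cannot be computed, and both appear to be sent to Cox and Kaplan–Meier although they are day counts

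*Protocol article*

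**What the plan says.** Section 2.6 (Outcome Measures) lists four secondary outcomes. Three matter here:

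- VFD is "defined as the number of days between successful weaning from mechanical ventilation and day 28 after ICU admission".
- RFFD is "defined as the number of days between a day without evidence of respiratory organ failure", with a literature reference attached.
- 28-day mortality is "all-cause mortality within 28 days following enrolment".

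Section 2.7 (Statistical Analysis) treats the three together: "VFD, RFFD and 28-day mortality will be screened indicators with LASSO-COX and RFE-SVM algorithm". The next sentence reads "Thereafter, these will be estimated using the Kaplan–Meier method". Earlier, the same section names the t test or the Wilcoxon rank sum test for continuous variables between two groups.

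Section 2.4 (Data Collection) shows that the case report form (CRF) holds "ventilator use or not" among the treatment items, and "intensive care unit (ICU) stay or not, length of ICU stay, total length of hospital stay, and in-hospital death" as outcomes. Section 2.1 plans follow-up until April 2023 and recruits 200 of the 400 patients retrospectively.

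**The concern.** VFD is meant to penalise both long ventilation and death. The printed definition depends only on the weaning day, so death after weaning costs nothing. It also needs a weaning date and an ICU admission date, which many patients with sepsis will not have. The comparison would then rest on a selected subset, namely those ventilated in the ICU and weaned. Within that subset, patients who died can rank above survivors.

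The analysis adds a separate difficulty. Cox regression and Kaplan–Meier need a time to an event and a rule for censoring. VFD and RFFD are counts for which more is better, and the article defines neither event nor censoring for them. A curve or hazard ratio for the high-risk against the low-risk group on these outcomes would have no clear meaning.

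**Working it through.** The documents give no sample size, power or event count for these outcomes, so there is no figure of the plan's own to reproduce. The check applies the definitions as printed.

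**1. VFD by type of patient.** Days are counted from ICU admission. Printed rule: VFD = 28 − weaning day. Comparison rule (an assumption, the usual composite): 0 if dead by day 28 or not weaned by day 28; 28 if alive and never ventilated; otherwise 28 − weaning day.

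| Patient | Printed rule | Composite rule |
|---|---|---|
| Weaned day 5, alive at day 28 | 28 − 5 = 23 | 23 |
| Weaned day 5, dies day 10 | 28 − 5 = 23 | 0 |
| Weaned day 20, alive at day 28 | 28 − 20 = 8 | 8 |
| Dies on the ventilator, day 6 | no value | 0 |
| Still ventilated at day 28 | no value | 0 |
| Never ventilated, alive | no value | 28 |

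In the second row, 28 − 10 = 18 of the 23 credited days fall after death.

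**2. Are patients without a value expected?** Yes. The CRF records ventilator use and ICU stay as yes or no (section 2.4). Neither is an entry criterion (section 2.2). The Discussion says that mild ARDS may not need invasive ventilation. The documents do not say how many such patients there will be. For illustration only, let v be the share ventilated and u the share of those never weaned. The number without a VFD is 400 × [(1 − v) + v × u]. With assumed v of 30–70% and u of 10–40%:

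- lowest: 400 × (0.30 + 0.70 × 0.10) = 148
- highest: 400 × (0.70 + 0.30 × 0.40) = 328

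**3. Effect on a group comparison.** This is a simulation with assumed inputs: two groups of 20,000, all ventilated, the same exponential weaning times (mean 8 days), deaths spread evenly over 28 days, and 28-day mortality of 15% against 30%, 40% or 50%.

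| Mortality compared | Mean VFD, printed rule | Mean VFD, death = 0 |
|---|---|---|
| 15% v 30% | 20.6 v 20.9 | 16.9 v 13.8 |
| 15% v 40% | 20.7 v 21.1 | 16.9 v 11.8 |
| 15% v 50% | 20.6 v 21.1 | 16.9 v 10.0 |

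Under the printed rule the group with more deaths looks slightly better. Patients who die before weaning drop out, so those left were weaned earlier, and deaths after weaning keep full credit.

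**4. RFFD.** The sentence gives one day where an interval needs two. It states no second endpoint, window or rule for death. Nothing can be calculated from it as printed.

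**5. VFD used as a survival time.** A second simulation used 1,000 patients per group with mean weaning times of 6 and 12 days, keeping those weaned before day 28. Slow against fast weaning gives a hazard ratio of 0.61 for time to weaning, and 1.51 when VFD itself is entered as the time. The direction reverses, and the supposed event is only the end of a count.

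**The case against.** A journal article condenses a longer protocol, and scoring rules for patients never ventilated or never in the ICU are often left to the analysis plan. That stands: silence on those patients alone would not be a finding. But the VFD definition is stated, and it assigns a high value to a patient who dies after weaning. A later document would have to override it, not just add detail.

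The wording of section 2.7 is loose. Two algorithms are named for three outcomes without allocation, and it is not certain what is to be estimated by Kaplan–Meier. The natural reading includes VFD and RFFD; at the least, the allocation is unclear. The Wilcoxon test already named in that section could be used for both, which makes the repair easier but does not remove the sentence that points elsewhere.

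Successful weaning is not defined and might require survival for some period. That would remove very early deaths after weaning, but not later deaths before day 28. The source cited for RFFD may contain a complete definition; the printed sentence still needs completing.

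A reader might go further in four ways that the documents do not support:

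- **That 28-day mortality also rewards death.** It does not: death is the event, and the definition is conventional.
- **That RFFD scores deaths well.** No score of any kind can be read from an incomplete sentence.
- **That 40 to 80 deaths would be mis-scored**, by applying the Introduction's mortality of about 40% to 100–200 ARDS cases (25–50% of 400). That mortality is a background figure, not labelled as 28-day, and only deaths after weaning and before day 28 count. The product is at best a ceiling.
- **That survivors would be informatively censored at discharge.** No such rule is stated, and follow-up to April 2023 runs about 11 months past the end of recruitment in May 2022.

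**Conclusion.** The point holds for VFD and RFFD. The VFD definition gives full credit to patients who are weaned and then die before day 28 (23 days, against 8 for a survivor weaned on day 20). It gives no value to patients never weaned, never ventilated or never in the ICU. How many patients either fault touches cannot be derived from the documents; 148 to 328 of 400 without a value, and the simulated means, rest on assumed rates. RFFD cannot be computed as printed. Cox and Kaplan–Meier results for either count would not be interpretable; this part rests on the natural reading of section 2.7.

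A minor related point concerns 28-day mortality. Its clock starts at enrolment, a date the article does not define for the 200 retrospective patients, and the listed CRF item is in-hospital death only.

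The matter is worth correcting before analysis, but it is confined to secondary outcomes. The prediction of ARDS and its sample size do not depend on it.

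**What to change.** 1. State one day 0 for VFD and RFFD that exists for every patient in both cohorts, for example the index CT or the date of sepsis diagnosis.
2. Define VFD as days alive and free of ventilation from day 0 to day 28, with 0 if dead by day 28 and 28 if alive and never ventilated. Complete RFFD in the same way for respiratory organ failure.
3. Compare VFD and RFFD between risk groups with the Wilcoxon test already in section 2.7, or use a proportional-odds model where covariates are needed.
4. Reserve LASSO-Cox and Kaplan–Meier for death, and say which method serves which outcome.
5. State the index date that serves as enrolment for the retrospective patients, and take day-28 vital status from the planned follow-up.

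The cost is revised wording in sections 2.6 and 2.7 and one CRF field for day-28 status. VFD will be lower wherever deaths now score 0, and some patients discharged before day 28 will have to be traced.
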